**HRB DIFA-2020-028**

**Study Protocol**

**1. Enhancing Men’s Awareness of Testicular Diseases (E-MAT): A Randomised Feasibility Trial**

**1.1 Aim:** In order to determine the processes needed to conduct a definitive trial, identify unforeseen problems, and plan for progression to a definitive trial, we will test the effect of E-MAT_VR_ (intervention) compared to E-MAT_E_ (control) on primary outcomes (testicular knowledge and self- examination behaviours) and secondary outcomes (testicular awareness, frequency of self-examination, recommendation of self-examination to others, help-seeking intentions, implementation intentions, and perceived risk) among GAA players and coaches. Outcomes (all self-reported) will be measured at baseline (T0), immediately post-test (T1), and three months post-test (T2) using electronic surveys.

**1.2 Inclusion criteria**

1. Biological males***.***
2. Members of the target GAA clubs since testicular injuries are common in field sports like hurling.
3. Residing in Ireland.
4. Aged 18-50 years (age group at risk for testicular diseases).

**1.3 Exclusion criteria**

1. History of seizures.
2. History of motion sickness.

**1.4 Setting**

Several GAA clubs are adopting “The Healthy Club” philosophy to improve the health of their members (https://www.gaa.ie/my-gaa/community-and-health/healthy-club/). Data will be collected in six geographically dispersed GAA clubs.

**1.5 Primary outcomes**

1. Testicular knowledge (Dichotomous)
2. Testicular self-examination behaviours (Dichotomous)

**1.6 Secondary outcomes**

1. Testicular awareness (Likert scale)
2. Frequency of testicular self-examination (Likert scale)
3. Recommendation of testicular self-examination to others (Likert scale)
4. Help-seeking intentions (Likert scale)
5. Implementation intentions (Likert scale)
6. Perceived risk of testicular disorders (Likert scale)

Outcomes will be measured at baseline (T0), immediately post-test (T1), and three months post-test (T2) using the Castor EDC software (https://www.castoredc.com/).

A Research Assistant and/or Research Support Officer will be present to ensure participant safety. There is no in-person follow-up. Participants will be contacted (phone call/text message/email) to ensure completion of outcome measurement at T2. Non-respondents and those who withdraw will be considered lost to follow-up. Retention is key to ensuring power and internal validity. This will be addressed in the SWAT described below.

**1.7 Sample size**

Given that the goal of a feasibility trial is to identify problems that would impede the conduct of a larger, definitive efficacy trial, we have set the sample size at 59 based on advice from [Viechtbauer et al. (2015)](https://pubmed.ncbi.nlm.nih.gov/26146089/) which is aimed at being able to detect failures in study processes that would occur just 5% of the time (with 95% confidence). Bearing in mind a potential attrition rate of 25-30%, 75-80 participants will be recruited.

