**1.8 Randomisation and allocation concealment**

For each of the six participating GAA clubs, individual participants will be randomised with the same probability to one of the two arms (E-MAT_VR_/E-MAT_E_). Allocation concealment will be maintained using a computerised system. Once participants have consented and their baseline assessment has been entered into the computer database, their allocation will be given by automated email. Randomisation and allocation concealment will be conducted according to the standard operating procedures (SOPs) of the Statistics and Data Analysis Unit of the HRB Clinical Research Facility-Cork (HRB CRF-C).

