**2. Mixed-Method Process Evaluation**

**2.1 Objectives**

1. Understand and mitigate potential sources of intervention failure in terms of contextual effects, inputs, engagement, activities, and outcomes.
2. Explore participants’ experiences of E-MAT_VR_ and E-MAT_E_ focusing on perceived effectiveness; feasibility of study and procedures; relations between implementation, mechanisms, and context; and barriers and facilitators to conducting a definitive trial.

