**2.6 Anticipated and unanticipated outcomes/Impact: Survey**

Participants will complete an online survey about their satisfaction (Likert scale) and experiences (open-ended) of participating. Other data that will be collected include timing and difficulties experienced with interventions, frequency of adverse events, and implementation problems.

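### The 5%/95% detection claim for 59 participants holds only for processes everyone goes through; for delivery of one arm's intervention the detectable rate is about 7-8%

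*Protocol*

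**What the plan says.** Protocol section 1.7 gives the purpose of the sample size: "the goal of a feasibility trial is to identify problems that would impede the conduct of a larger, definitive efficacy trial". It then says "we have set the sample size at 59" and gives the property this number is meant to have: it is "aimed at being able to detect failures in study processes that would occur just 5% of the time (with 95% confidence"). For recruitment it adds: "Bearing in mind a potential attrition rate of 25-30%, 75-80 participants will be recruited". These are totals for the trial. Nothing in the section limits the detection property to processes that both arms share.

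Section 1.8 says that "individual participants will be randomised with the same probability to one of the two arms".

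Section 2 makes delivery problems an object of study. The first objective in section 2.1 is to "Understand and mitigate potential sources of intervention failure in terms of contextual effects, inputs, engagement, activities, and outcomes". Section 2.3 plans observation of whether delivery follows the agreed method. The survey in section 2.6 collects "timing and difficulties experienced with interventions, frequency of adverse events, and implementation problems". Section 2.9.1 presents the quantitative process data by allocation arm.

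**The concern.** A problem-detection sample size counts opportunities: each exposed participant is one chance for a failure to show itself. Consent, baseline entry, allocation and the electronic surveys give every participant such a chance. Delivery of E-MAT VR does so only for those allocated to it, and the same is true of delivery of the control. For these processes about half the trial is exposed, and the 5%/95% property does not carry over.

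At stake is how an absence of problems is read. If no delivery problem is seen in one arm, section 1.7 taken at face value suggests that rates of 5% or more have been ruled out with 95% confidence. The number exposed in one arm does not support that. The question bears on whether to progress to a definitive trial, and the process data are to be summarised by arm.

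**Working it through.** **Inputs**
- Sample size 59, failure rate 5%, confidence 95%: section 1.7.
- Recruitment 75-80 in total: section 1.7.
- Two arms, equal allocation probability: section 1.8.

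**Step 1: reproduce 59.** The protocol does not print a formula. The standard one asks for the smallest n such that 1 - (1 - p)^n is at least 0.95.
- n = ln(0.05) / ln(0.95) = 58.40, rounded up to 59.
- Check: 1 - 0.95^59 = 0.9515, and 1 - 0.95^58 = 0.9490.

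The plan's figure is reproduced exactly, with n being the number exposed to the process.

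**Step 2: number exposed to one arm's delivery.** Half of 75 is 37.5 and half of 80 is 40, so about 37-40 per arm. Delivery precedes the three-month follow-up, so the number allocated is used, without a deduction for attrition.

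**Step 3: chance of seeing at least one 5% failure in one arm.**
- 37 exposed: 1 - 0.95^37 = 0.850.
- 40 exposed: 1 - 0.95^40 = 0.871.

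The chance of missing such a failure is therefore about 13-15%, against the 5% implied by section 1.7.

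**Step 4: rate detectable with 95% confidence in one arm.** Solve 1 - (1 - p)^m = 0.95 for p, giving p = 1 - 0.05^(1/m).
- m = 37: p = 7.8%.
- m = 40: p = 7.2%.

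The same numbers are the one-sided 95% upper limits for the true rate when no failure is seen among 37 or 40 people.

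**Step 5: does an exact half matter?** Section 1.8 fixes equal probability, not equal arm sizes. If each participant falls in a given arm with probability 0.5, the chance of seeing a 5% failure specific to that arm is 1 - (1 - 0.5 × 0.05)^N.
- N = 75: 0.850.
- N = 80: 0.868.

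The answer is unchanged for practical purposes.

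**Step 6: what the unqualified property would require.** Having 59 exposed in each arm means 2 × 59 = 118 in total, against 75-80 recruited. So 59 cannot be meant as a per-arm figure.

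**The case against.** The best defence is that section 1.7 says nothing false. The number 59 is correct, and many processes (consent, baseline entry, automated allocation, electronic surveys, reminders) involve every participant. The section makes no statement about separate arms, so the narrower reading could be the intended one. The arithmetic part of this stands: 59 is not a calculation error. The defence does not settle the scope, because the statement is unqualified, is tied to problems that would impede a definitive trial, and sits beside an evaluation of intervention failure and delivery.

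Four stronger readings are tempting and are not supported:

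- *That the gap concerns VR only.* Sections 2.1 and 2.6 cover participants and interventions in both arms. The limit applies equally to failures specific to the control.
- *That the shortfall is larger still at three months, because of attrition.* Section 1.6 describes no in-person follow-up, only completion of outcome measures with contact by phone, text or email. No arm-specific delivery is described at that point, so the number allocated is the relevant one.
- *That failures at club level are also covered by the claim and badly under-detected with six clubs.* Section 1.7 makes no club-level claim.
- *That the team will report 95% confidence in a rate below 5% after seeing no problems in one arm.* No section plans such a statement. Section 2.9.1 promises descriptive summaries by arm, which would show the denominators. The risk is that a reader applies section 1.7 to those summaries.

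**Conclusion.** The concern holds as a matter of scope. The 5%/95% property is right for a process that 59 participants go through. For a failure specific to delivering one arm's intervention, the design gives about an 85-87% chance of seeing a 5% failure, and a rate detectable with 95% confidence of about 7.2-7.8%.

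This rests on three assumptions: recruitment reaches 75-80, about half of those recruited are allocated to each arm and receive its intervention, and failures are independent between participants. If some allocated participants never receive the intervention, the detectable rate rises.

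The size is modest for a feasibility trial. It does not call the choice of 59 into question and gives no reason to enlarge the trial. It does limit what an absence of delivery problems in one arm can show.

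**What to change.** In section 1.7, limit the 5%/95% statement to processes shared by both arms, when 59 participants are exposed to them. Then add one sentence, for example: *For processes specific to delivering one arm's intervention, about 37-40 participants per arm are exposed, and the failure rate detectable with 95% confidence is about 7-8%; a zero count of problems in one arm will be read against this bound.*

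The condition that 59 are exposed should stay in the wording. Recruiting 75 with 30% attrition leaves 75 × 0.70 = 52.5, and 1 - 0.95^52 = 93.1%, so an unconditional 95% would not hold for a shared process assessed after attrition.

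The cost is a small edit to the text. No participants, procedures or analyses change; the stated figure becomes less favourable. The alternative, securing 5%/95% within each arm, would need 118 exposed in total and is out of proportion to the problem.

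### Section 1.7: recruiting 75-80 does not secure the required 59 retained participants over the full stated 25-30% attrition; 79 to 85 would be needed

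*Protocol*

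**What the plan says.** Protocol section 1.7 rests the sample size on feasibility alone. It says "we have set the sample size at 59", a number described as "aimed at being able to detect failures in study processes that would occur just 5% of the time (with 95% confidence". The next sentence turns this into a recruitment target: "Bearing in mind a potential attrition rate of 25-30%, 75-80 participants will be recruited". No inflation formula is given.

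Section 1.6 defines who counts as lost: "Non-respondents and those who withdraw will be considered lost to follow-up". It places the final assessment (T2) three months after the intervention, by remote contact only.

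**The concern.** Enlarging 59 to allow for attrition makes sense only if 59 is the number meant to remain. It is also a threshold without slack: 58 participants already give less than 95% confidence. The recruitment target should therefore leave at least 59 at every attrition rate that the section names. It does so in only a small part of that range.

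The 5%/95% property is the only justification the protocol gives for its size. If the target does not deliver it on the protocol's own inputs, the stated assurance is slightly too favourable for whatever can be seen only in those still taking part at T2.

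**Working it through.** **Inputs, all from section 1.7:** problem frequency 5%; confidence 95%; required number 59; attrition 25% to 30%; recruitment 75 to 80.

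**Step 1. Reproduce the 59.** The chance of seeing a problem of frequency 5% at least once in n participants is 1 - 0.95^n. Setting this to at least 0.95 gives n ≥ ln(0.05)/ln(0.95) = 58.4, so 59. Check: n = 58 gives 94.90% and n = 59 gives 95.15%. The plan's figure reproduces exactly.

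**Step 2. Number to recruit so that 59 remain**, N = 59/(1 - attrition):
- 25% attrition: 59/0.75 = 78.7, so 79.
- 30% attrition: 59/0.70 = 84.3, so 85.

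The stated 75-80 is 4 below the first figure at its lower end and 5 below the second at its upper end.

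**Step 3. What 75-80 leaves at T2**, N × (1 - attrition), with the detection probability for whole participants, rounded down:

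| Recruited | Attrition | Retained | Chance of seeing a 5% problem |
|---|---|---|---|
| 75 | 25% | 56.25 (56) | 94.3% |
| 75 | 30% | 52.5 (52) | 93.1% |
| 80 | 25% | 60 | 95.4% |
| 80 | 30% | 56 | 94.3% |

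Three of the four corners fall below 59. At 30% attrition no number from 75 to 80 is enough. At 25%, 79 or 80 is enough (79 × 0.75 = 59.25) and 78 is not (58.5).

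**Step 4. Attrition that still leaves 59**, 1 - 59/N: with 75 recruited, 1 - 59/75 = 21.3%; with 80 recruited, 1 - 59/80 = 26.25%. The first lies below the whole stated range, and the second covers only its lowest part.

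**Step 5. Problem frequency detectable with 95% confidence**, 1 - 0.05^(1/m) for m retained: 5.5% in the worst corner (m = 52.5) and 4.9% in the best (m = 60), against the intended 5%.

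**Step 6. Processes observed in everyone recruited:** 1 - 0.95^75 = 97.9% and 1 - 0.95^80 = 98.3%. Both are above the 95% target.

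**The case against.** The strongest reply is that the property in section 1.7 concerns study processes, and most of these do not depend on T2 completion. Consent, baseline entry and automated allocation (section 1.8) and intervention delivery with its fidelity observation (section 2.3) come before any T2 loss. An unanswered T2 contact is itself an observed process event, and non-completers are invited to interview (section 2.7). For all of these the denominator can be larger than the T2 completers, and at the full 75-80 it is more than sufficient. The attrition range is also a rounded guess, and the worst corner loses about 2 percentage points of detection probability. All of this stands, and it limits the consequence to problems visible only among T2 completers. It does not make the three figures in section 1.7 agree.

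A reader might go further than the documents allow in three ways:

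- **A cause.** It is tempting to infer that 59 was multiplied by 1.25-1.30 instead of divided by 0.75-0.70. Multiplication gives 73.75 to 76.7, that is 74 to 77. This is close to 75 but does not yield 80, and 80 fits 59/0.75 = 79 rounded up at least as well. The protocol shows no working, so neither explanation can be asserted.
- **A universal shortfall.** Recruiting 79 or 80 with 25% loss does retain 59.
- **A loss of power for the primary outcomes.** Section 1.6 links retention to power, but section 1.7 bases 59 on no hypothesis test or power calculation for those outcomes. The discrepancy has no bearing on a stated power.

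**Conclusion.** The point holds as a minor arithmetic inconsistency. On the protocol's own inputs, a target of 75-80 leaves about 52-60 participants at T2 and secures 59 over only a small part of the 25-30% attrition range; 79 to 85 would be needed. The consequence is a detection probability of about 93-95% instead of at least 95% for a 5% problem seen only among T2 completers, while processes seen in all recruits reach about 98%. The validity of the estimates and the conduct of the trial do not depend on it.

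This rests on three assumptions: that 59 is the number to be retained, as its enlargement for attrition implies; that attrition is applied as a fixed proportion of those recruited; and that problems occur independently across participants, as the calculation behind 59 already requires.

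**What to change.** Keep the recruitment target and restate the last sentence of section 1.7, for example: *We will recruit 75-80 participants. With 25-30% attrition, about 52-60 are expected at T2, which gives a probability of about 93-95% of observing at least once a problem that occurs in 5% of participants. At least 59 will be retained only if attrition does not exceed 21% (75 recruited) to 26% (80 recruited). For processes observed in all recruits the probability is about 98%, which meets the 95% target.*

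This changes one sentence and needs no extra participants. The downside is a slightly less favourable stated figure for T2.

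If the team prefers to guarantee 59 at T2 over the whole stated range, the target would have to be 85 (85 × 0.70 = 59.5), which is 5 more than the present upper figure. Given the small gain, the restatement is sufficient.

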**1.8 Randomisation and allocation concealment**

For each of the six participating GAA clubs, individual participants will be randomised with the same probability to one of the two arms (E-MAT_VR_/E-MAT_E_). Allocation concealment will be maintained using a computerised system. Once participants have consented and their baseline assessment has been entered into the computer database, their allocation will be given by automated email. Randomisation and allocation concealment will be conducted according to the standard operating procedures (SOPs) of the Statistics and Data Analysis Unit of the HRB Clinical Research Facility-Cork (HRB CRF-C).

**1.9 Blinding**

Given the differences between the two arms, participants will be aware of the arm they have been randomised into. Outcome assessments will be self-reported and returned to research staff with no information on allocation. Blinding will be maintained throughout data analysis. Unblinding will be facilitated by the independent statistician following completion of the protocol-specified data analysis.

**1.10 Data analysis**

Analyses will be conducted by the lead statistician, under the SOPs of the Statistics and Data Analysis Unit of the HRB CRF-C. Before recruitment, a detailed Statistical Analysis Plan will be uploaded alongside the study protocol to the relevant registries. Data will undergo extensive quality checking and potential errors will be verified from source data *a priori.*

Analyses of outcomes will be conducted on an intention-to-treat basis. Differences in outcomes by study arm, over time, will be estimated using generalised linear mixed effects models with the appropriate link function (based on the distribution of the outcome or expected error distribution). We will report minimally adjusted models, which will include effects of intervention arm and time. We will report a fully adjusted model that includes the key predictor variables collected at baseline. Missing data will be evaluated and addressed using appropriate methods (e.g., multiple imputation or inverse-probability weighting). Effect estimates for all pre-specified primary and secondary endpoints, will be publicly reported with 95%CI and exact p-values, in accordance with recent guidance from the American Statistical Association [19].

Analyses will be conducted using transparent, open-science tools. All analysis steps, including cleaning or modifications to study database, will be fully scripted and replicable. Scripts for the key analyses will undergo testing prior to data analysis. Upon completion, the study database will be prepared according to FAIR data principles and be made available along-side the analysis scripts.

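### Participants are randomised within each of six clubs, but the terms named for the minimally adjusted model are arm and time only, so that model as written does not reflect the club-based randomisation

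*Protocol*

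**What the plan says.** Protocol section 1.4 sets the trial in six clubs: "Data will be collected in six geographically dispersed GAA clubs". Section 1.8 ties allocation to club: "For each of the six participating GAA clubs, individual participants will be randomised with the same probability to one of the two arms". It names neither stratification nor a block scheme.

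Section 1.10 says that differences by arm over time will be "estimated using generalised linear mixed effects models with the appropriate link function". It then describes two models. For the first: "We will report minimally adjusted models, which will include effects of intervention arm and time". For the second: "We will report a fully adjusted model that includes the key predictor variables collected at baseline". Club is named in neither, no random effect is specified for either, and neither is called the main model. The section refers to a fuller document: "Before recruitment, a detailed Statistical Analysis Plan will be uploaded alongside the study protocol to the relevant registries". That document is not at hand.

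Section 1.5 lists two primary outcomes, both dichotomous. Outcomes are measured at baseline (T0), immediately post-test (T1) and three months post-test (T2).

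**The concern.** When allocation is carried out and balanced within groups, the grouping is part of the design and the analysis should carry it. If it does not, differences between groups cancel out of the arm contrast but stay in the model's estimate of unexplained variation. The model then reports more uncertainty than the design produces.

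Here the protocol gives a list of terms for the minimally adjusted model, and club is not on it. An SAP that followed the list literally would leave club out; one that added club would depart from the protocol wording. The mixed-model label does not settle the matter. With three measurements per man, the natural random effect is participant, and a participant intercept alone leaves club differences inside the between-participant variance.

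At stake is some precision and power in effect estimates that section 1.10 promises to report with 95% confidence intervals and exact p-values.

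**Working it through.** **The plan's own figure.** Section 1.7 sets the sample size to "detect failures in study processes that would occur just 5% of the time (with 95% confidence". The calculation is n = ln(1 − 0.95)/ln(1 − 0.05) = 58.40, rounded up to 59. The chance of seeing at least one such failure is 0.9515 with 59 and 0.9490 with 58. The figure reproduces. It does not involve club or the outcome model, so this point changes no stated number.

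**Inputs.** From the protocol: six clubs and 1:1 allocation within club. Assumed: 60 men analysed (80 recruited less 25% attrition = 60), 10 per club. The club ICC is not in the protocol, so a range is used.

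**Continuous outcome, one visit, allocation balanced 5:5 in each club, total SD 1.** Club effects cancel from the arm difference, so the correct variance is (1 − ICC)(1/30 + 1/30). The model without club estimates the residual variance with 58 degrees of freedom. Club differences within each arm add an expected sum of squares of 5 × 5 × ICC, or 50 × ICC over both arms. The estimated variance is therefore (1 − ICC) + (50/58) × ICC, and the ratio of standard errors is

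sqrt{[(1 − ICC) + 0.862 × ICC]/(1 − ICC)}.

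- ICC 0.05: sqrt(0.9931/0.95) = 1.022
- ICC 0.10: sqrt(0.9862/0.90) = 1.047
- ICC 0.20: sqrt(0.9724/0.80) = 1.103

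Simulation (8,000 runs per cell; club as a fixed effect; power for an assumed difference of 0.7 SD) agrees:

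| ICC | SE without / with club | Type I error without / with | Power without / with |
|---|---|---|---|
| 0 | 0.257 / 0.257 | 0.046 / 0.046 | 0.763 / 0.760 |
| 0.05 | 0.256 / 0.251 | 0.046 / 0.050 | 0.772 / 0.784 |
| 0.10 | 0.255 / 0.244 | 0.042 / 0.052 | 0.777 / 0.806 |
| 0.20 | 0.253 / 0.230 | 0.033 / 0.050 | 0.796 / 0.845 |

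**Dichotomous outcome, one visit, logit link (assumed), same layout.** The standard error of the log odds ratio moves the other way. In one scenario at the lowest ICC tried (0.02) it was 0.522 without club and 0.553 with it (0.553/0.522 = 1.06). In one at ICC 0.10 it was 0.552 and 0.601 (1.09). The coefficient grows by more than its standard error, because omitting a prognostic factor pulls the odds ratio toward 1. Power therefore rises with club: 0.41 to 0.45 in one scenario, and by about 4 to 8 points for an odds ratio of 3 over ICC 0.02 to 0.20. Part of that gain persists when no club variation is simulated, because a fixed-effect logistic model with 10 men per club overstates the coefficient. The gain is better read as a few points. Type I error without club was 0.038 to 0.052 over ICC 0.02 to 0.10, and about 2.5% to 4% at ICC 0.10 to 0.20 in a separate set of runs.

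**Change from baseline.** Stable club differences cancel. The simulated standard error for a continuous change was 0.257 with and without club at ICC 0.10.

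**Simple 1:1 allocation within club.** Type I error without club stays at 0.048 to 0.053 at every ICC. A fixed club effect then costs precision at small ICC (SE 0.259 without, 0.268 with, at 0.02), breaks even at 0.10 (0.257 and 0.257), and gains only at 0.20 (0.255 and 0.243).

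**The case against.** The strongest reply is that model terms belong in the SAP, that an SAP is promised before recruitment, and that the protocol excludes nothing. Club could be one of the unnamed random effects, or one of the key predictors in the fully adjusted model. This stands against any claim about the whole analysis. A reader might infer that the trial's main analysis ignores its randomisation strata. The protocol does not support that, because it designates no main model and leaves the random effects and key predictors open. The reply does not dispose of the point, since the minimally adjusted model is described by its terms and club is absent from them.

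Second, section 1.8 mentions no blocking. If allocation is simple within each club, doing it club by club places no constraint on it, and inference without club is valid. This stands; the stated loss depends on balance within club, which is a reasonable reading but an assumption.

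Third, section 1.10 estimates differences over time. If the arm effect is read as change from baseline, stable club differences largely drop out. This also stands, although the protocol does not spell out the contrast.

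Fourth, a reader might argue that men in a club must be correlated through shared delivery arrangements. The protocol does not document this: section 1.6 says only that a research assistant and/or support officer will be present. The size of any club effect remains an assumption.

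Finally, the sample size rests on detecting process failures, so the arm comparison is not what the trial is sized for. That limits the importance of the point.

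**Conclusion.** The point holds for the minimally adjusted model as written: its named terms omit the grouping by which participants are randomised. The consequence is modest. If allocation is balanced within club, inference is slightly conservative. For a continuous single-visit outcome, standard errors are about 2% to 5% too wide at an assumed ICC of 0.05 to 0.10. For the dichotomous primary outcomes under a logit link, the odds ratio is attenuated and power is a few points lower.

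It would be wrong to infer false-positive results. Type I error without club is at or below about 5% with balanced allocation and unaffected with simple allocation. It would also be wrong to carry the claim of too-wide standard errors over to the primary outcomes, where the log-odds-ratio standard error is smaller without club.

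These sizes rest on assumed ICCs, about 60 men analysed and a single-visit comparison; for change from baseline the effect is smaller or absent. This is a worthwhile, low-cost correction, and the sample size is unaffected.

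**What to change.** Amend section 1.10 along these lines: both the minimally and the fully adjusted models will include club and a participant random effect; club enters as a random intercept, or as a fixed effect where the outcome counts per club allow. The SAP should carry the same wording.

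The change is to analysis text only, but it has statistical costs:

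- A fixed club effect uses up to five degrees of freedom (six clubs less one).
- With about 10 analysed men per club, binary outcomes may be sparse. At an assumed 20% control risk, 17% to 61% of simulated trials had at least one club with no variation in the outcome. This favours the random intercept for the primary outcomes.
- If allocation turns out to be simple within club and club differences are small, a fixed effect loses a little power: 0.760 without club and 0.728 with it at ICC 0.02, for the 0.7 SD difference.

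Between-club variation can be reported descriptively to help plan the definitive trial, with the caution that six clubs estimate it imprecisely.
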